### Play Active program for ECEC

The Play Active program consists of an evidence-informed editable physical activity policy template containing nine recommendations, two key statements and 25 practices and six policy implementation support strategies.

#### Development of the program

Play Active was developed in consultation and co-produced [29] with formal and informal study partners including representatives from ECEC service providers, ECEC professional associations, government (health; local government, sport and cultural industries) and non-government organisations (National Heart Foundation, Cancer Council Western Australia, Nature Play Australia) all focused on promoting children’s physical activity. Educators have provided critical input to the Play Active program development and implementation support strategies through prior formative qualitative research. Parents provided input to the Play Active program development, implementation and evaluation via a Consumer Reference Group which meets quarterly.

The physical activity policy template was developed using a modified three round Delphi methodology; full details of the methods have been published previously [13]. The policy template aligns with national and international 24-h movement guidelines and provides age-specific guidelines on the amounts of physical activity and sedentary time, including screen time, young children should do while attending ECEC. The policy template includes 25 educator-related physical activity practices which were identified through focus groups with educators and the Delphi process.

#### Physical activity policy template

ECEC directors will be provided via email with an editable version (word document) of the physical activity policy template, which includes:Two key statements which apply to all children and nine recommendations that are age-specific (see Table 2 for details)25 practices (known as procedures in the ECEC context) outline specific opportunities to achieve the recommendations and are specific to management and educators (14 practices), the physical environment (four practices), parent and carer engagement (five practices), and policy monitoring and review (two practices) [13].

**Table 2 Tab2:** Key statements and recommendations in the Play Active policy template [13]

Key statement	Recommendation	Age group		
		Infants (under 1 year)	Toddlers (1–2 years)	Kindergarten (3–5 years)
Encourage physical activity in young children	To meet the Australian 24-h movement guidelines for the early years, provide children with at least 180 min of physical activity daily, via a variety of physical activities spread throughout the day. More is better	˟	✓	✓
	For kindergarten children, this will include at least 30 min of energetic play each day at ECEC. More is better	˟	˟	✓
	For infants who are mobile provide physical activity in a variety of ways, mainly through supervised, interactive floor-based play such as crawling and games. More is better	✓	˟	˟
	For infants not yet mobile, provide at least 30 min of tummy time spread throughout the day, including reaching and grasping, pushing and pulling	✓	˟	˟
Limit sedentary behaviours in young children	Toddlers and kindergarten children will not be confined for more than 60 min at a time (e.g., in a stroller or highchair). Children will not sit for extended periods (expect when engaged with a caregiver in an activity, e.g., reading and storytelling). Less is better	˟	✓	✓
	Sedentary screen time for purposes other than learning will not be allowed	˟	✓	✓
	Screen time for infants is NOT recommended	✓	˟	˟
	Ensure cots, car seats, and highchairs are used for their primary purpose only (cots for sleeping, car seats for vehicle travel, and highchairs for eating)	✓	˟	˟
	Limit the use of equipment such as strollers, swings, and bouncer seats/chairs for holding infants while they are awake	✓	˟	˟

#### Policy implementation supports

Alongside the physical activity policy template, directors will be provided with six implementation support strategies. The itemised components of each implementation support strategy are detailed in Additional file 2 and summarised below.(i)Personalise policy: ECEC service staff will be encouraged to personalise the physical activity policy template to suit their service and the needs of their attending children and families. Services are asked to *select at least five from 25 practices* to prioritise during initial implementation. To support ECEC services in this, seven high impact and low effort practices, based on previous testing [13] are indicated.(ii)Policy review and approval: Services are asked to submit their draft physical activity policy (based on the template) to Play Active. Two Play Active Project Officers independently review the policy and approve policies that meet minimum criteria. The minimum requirements for physical activity policies to be approved are that it include: two (out of two) key statements; nine (out of nine) recommendations; and at least five (out of 25) practices to prioritise implementing during the trial’s intervention period. After service’s physical activity policies have been approved as meeting the minimum requirements, services will be provided with the remaining implementation support strategies to assist with policy implementation and encouraged to implement the policy over a minimum period of 3 months. Services will be granted a period of up to 2 months for personalising and submitting physical activity policies for approval. After 2 months, any services that do not submit a physical activity policy for review and approval will be provided with all policy implementation supports. Personalisation of the policy and the policy review process is important to enhance policy ownership and implementation of the policy within each service. This process aligns with standard practice in ECEC service’s when initiating and implementing any new policy.(iii)Resource guide: An evidence-informed resource guide (hard copy and digital PDF) with practical tips describing how to implement each of the 25 physical activity practices into daily practice has been developed. The resource guide consists of the following sections: glossary of terms; policy template; benefits of being an accredited Play Active service; and a section covering each of the 25 practices. The 25 practices are consistent with the policy template and outline practical strategies educators can use, an evidence-informed explanation of what it means, and various evidence-based helpful resources for more information. One physical copy of the resource guide is provided to each service as well as an electronic copy.(iv)Brief assessment tool: A brief monitoring tool has been created for educators to monitor children’s physically activity whilst attending ECEC. The Energetic Play Assessment Tool was adapted from a brief instrument developed by Rice and colleagues [30]. For each child, educators record how much of a typical day in the last month was spent energetically playing (e.g., running, jumping, skipping, dancing, riding, climbing and energetic games) indoors and outdoors. There are five response options (very rarely energetic, rarely energetic, sometimes energetic, often energetic, very often energetic) recorded across four parts of the day (arrival to morning tea, morning tea to lunch, lunch to afternoon tea, afternoon tea to departure). Reliability and validity of the tool is currently being assessed. The tool is included as part of the resource guide.(v)Professional development: Training to upskill educators in providing more physical activity opportunities for children in their care, including specific skills on developing fundamental movement skills and active play-based learning. The training for educators will be made available by study partners (Nature Play WA and KIDDO). The Nature Play WA training involves five self-paced centre-based e-learning modules with associated resources. Each module has up to 40 segments of content, equates to 3–4 h of training per module and is expected to take at least 6 weeks to be completed. As part of the trial there is a cost of $99 per module per service. The module topics include: the importance of being a playful educator; active and playful outdoor learning environments; using outdoor play to increase physical activity; planning cycles for active outdoor play; and documenting as a process of reflection, intention and communication. The KIDDO professional development training will be provided to services for free as part of the trial and focusses on developing children’s physical literacy (fundamental movement skills). It involves six, 30–60-min online training modules which individual educators complete at their own pace. Module topics cover the importance of physical literacy; what are fundamental movement skills; teaching fundamental movement skills in early childhood; active ECEC environments; physical literacy in ECEC; and promoting motivation in children. The research team has shown in pilot studies that both professional development training options are feasible and effective in improving educators’ self-efficacy to engage children to be physically active in ECEC [24].(vi)Project Officer implementation support: including both weekly follow-up (phone and/or email) to complete the policy review and a mid-implementation prompt (phone call) to determine whether policy implementation has commenced. Service directors will be provided weekly email and phone call reminders to return their policy for review for up to 2 months.

### Wait-listed comparison

Services allocated to the wait-listed comparison group will be instructed to continue their usual practices around physical activity for the duration of the trial. After the conclusion of the post-intervention data collection, wait-listed comparison services will be provided with a copy of the Play Active physical activity policy template and the six policy implementation supports.

### Participant characteristics

Demographic information will be collected from directors and educators at baseline and will include age, gender, education, position title, months/years of experience working in current ECEC service, and months/years of experience working in ECEC sector. In addition, educators will be asked the name of the room they work in, the age/s of children in this room, and the number of hours per week usually spent working in this room.

### Primary outcomes

Change in educator physical activity practices related to the frequency or amount of time provided each day for physical activity, sedentary and screen time of young children in care will be assessed using established items drawn from existing validated instruments (e.g., Nutrition and Physical Activity Self-Assessment for Child Care (NAPSACC) [31] and Environment and Policy Assessment and Observation (EPAO) – Self Report tool [32]), which have been modified for the Australian ECEC context [27] and found to have acceptable test-retest reliability [33]. The measures align with the nine recommendations outlined in the editable policy template (see Table 3 for detail) and include educator-reported time provided each day for outdoor physical activity, indoor physical activity, educator-led physical activity, energetic play, tummy time (infants only), sitting time, screen time and daily frequency of outdoor play time.

**Table 3 Tab3:** Primary outcome measures corresponding to Play Active policy template recommendations

Recommendation	Educator survey items^a^	Response option
To meet the Australian 24-h movement guidelines for the early years, provide children with at least 180 min of physical activity daily, via a variety of physical activities spread throughout the day. More is better	The amount of time I provide children for indoor physical activity each day is	Seven categories: < 30 min; 30–59 min; 60–89 min; 90–119 min; 120–149 min; 150–179 min; ≥180 min
	The amount of time I provide children for outdoor physical activity each day is	Seven categories: < 30 min; 30–59 min; 60–89 min; 90–119 min; 120–149 min; 150–179 min; ≥180 min
	I provide children with outdoor play time	Six categories: 0 times per day; 1 time per day; 2 times per day; 3 times per day; 4 times per day; 5+ times per day
	The amount of educator led physical activity I provide children each day is	Seven categories: < 30 min; 30–59 min; 60–89 min; 90–119 min; 120–149 min; 150–179 min; ≥180 min
For kindergarten children, this will include at least 30 min of energetic play each day at ECEC. More is better	The amount of time I provide to children for energetic play each day is	Five categories: < 15 min; 15–29 min; 30–44 min; 45–59 min; ≥60 min
For infants who are mobile provide physical activity in a variety of ways, mainly through supervised, interactive floor-based play such as crawling and games. More is better	I provide infants and babies with supervised interactive floor-based play, including crawling and games	Seven categories: Never; rarely; sometimes; often; very often; always; not applicable
For infants not yet mobile, provide at least 30 min of tummy time spread throughout the day, including reaching and grasping, pushing and pulling	I provide non-crawling infants with tummy time each day for a total of	Six categories: < 15 min; 15–29 min; 30–44 min; 45–59 min; ≥60 min; not applicable
Toddlers and kindergarten children will not be confined for more than 60 min at a time (e.g., in a stroller or high chair). Children will not sit for extended periods (expect when engaged with a caregiver in an activity, e.g., reading and storytelling). Less is better	Outside of sleep and meal times, the longest children in my care are expected to remain seated at any one time is	Seven categories: < 10 min; 10–19 min; 20–29 min; 30–39 min; 40–49 min; 50–59 min; ≥60 min
Sedentary screen time for purposes other than learning will not be allowed	The amount of screen time I provide each day to children is	Six categories: 0 min; 1–14 min; 15–29 min; 30–44 min; 45–59 min; ≥60 min
Screen time for infants is not recommended		
Ensure cots, car seats, and high chairs are used for their primary purpose only (cots for sleeping, car seats for vehicle travel, and high chairs for eating).	I use cots, car seats and high chairs for their primary purpose only (cots for sleeping, car seats for vehicle travel, and high chairs for eating)	Six categories: Never; rarely; sometimes; often; very often; always
Limit the use of equipment such as strollers, swings, and bouncer seats/chairs for holding infants while they are awake	I use strollers, swings and bouncer chairs to hold infants while they are awake	Seven categories: Never; rarely; sometimes; often; very often; always; not applicable

^a^Items align with nine recommendations in the ECEC physical activity policy template and are based upon existing items [31–33]

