This paper describes the protocol of a pragmatic cluster randomised trial to evaluate the effectiveness of the Play Active physical activity policy intervention (with implementation support strategies) on increasing the frequency and amount of time each day ECEC educators provide for young children’s physical activity, sedentary and screen time (primary aim). Secondary aims will examine the effects of the intervention on:Educator physical activity practices, specifically increasing modelling of physical activity, programming and planning physical activity, and promoting and encouraging physical activity, and decreasing use of physical activity for managing misbehaviour.Increasing the proportion of ECEC educators who report a positive attitude, feel confident and motivated, feel supported by management and co-workers, and have a supportive physical space for promoting young children’s physical activity.The proportion of ECEC services with staff who take up and complete physical activity-related professional development and training.

The protocol follows the SPIRIT guidelines (Additional file 1) [25].

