**Table 1 Tab1:**
[figure not shown]
Schedule of enrolment, intervention, and assessments for the evaluation of the Play Active policy intervention and implementation support

Primary outcomes: educator-reported frequency and amount of time per day provided for children’s physical activity, sedentary and screen time. Secondary outcomes: educator physical activity practices, self-efficacy, motivation, attitudes and beliefs, social support, supportive physical environment and professional development training. ^1^For services allocated to intervention group only

The setting for this pragmatic trial are ECEC long-day care services, which provide centre-based childcare by professional staff for large groups of young children prior to formal compulsory schooling [27]. In Australia, ECEC long-day care services are mostly privately owned by providers, with the vast majority of providers approved to operate a single service only (81%), requiring enrolment and a daily fee for service [28]. ECEC services are highly regulated; the Australian National Quality Framework for ECEC outlines minimum standards across seven quality areas, including quality area 2.1.3 which states ‘healthy eating and physical activity are promoted and appropriate for each child’ [15]. As of February 2021, the regulating body, the Australian Children’s Education and Care Quality Authority reported there were 557 ECEC long-day care services located in the Perth and Peel metropolitan region of Western Australia. As the National Quality Framework also sets out minimum educator to child ratio requirements for ECEC services, there was an average of 66 approved places for children per service in the study region (range = 13–223 children).

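### Daily sedentary time is declared a primary outcome, but the only seated-time item records the longest single bout; the screen item measures daily screen time but cannot isolate the non-learning use that the policy bars

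*Protocol article*

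**What the plan says.** The Table 1 legend declares "Primary outcomes: educator-reported frequency and amount of time per day provided for children’s physical activity, sedentary and screen time". The Primary outcomes section repeats this as "frequency or amount of time provided each day for physical activity, sedentary and screen time of young children in care". It then gives the measures of educator-reported daily time, and that list includes "energetic play, tummy time (infants only), sitting time, screen time and daily frequency of outdoor play time".

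Table 3 gives the wording of the items. The seated-time item is "Outside of sleep and meal times, the longest children in my care are expected to remain seated at any one time is", with seven categories from under 10 min to 60 min or more. Its paired recommendation limits confinement to 60 min at a time and discourages long sitting, with an exception for sitting with a caregiver for something like a story. The screen item is "The amount of screen time I provide each day to children is", with six categories from 0 min to 60 min or more. It is paired with two recommendations: for toddlers and kindergarten children, "Sedentary screen time for purposes other than learning will not be allowed"; for infants, a recommendation against any screen time.

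On the fit between items and policy, the section states: "The measures align with the nine recommendations outlined in the editable policy template". The Background words the primary aim as "increasing the frequency and amount of time each day ECEC educators provide for young children’s physical activity, sedentary and screen time (primary aim".

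**The concern.** The declared quantity is a daily amount, and the sitting item returns a maximum. A maximum does not determine a total, and no analysis plan can recover a quantity that the survey does not ask for. If the outcome keeps its present label, the trial could report an effect, or no effect, on daily sedentary time without having measured it.

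The second issue is the claim that the measures align with the recommendations. For toddlers and kindergarten children the policy bars only part of screen use, while the item counts all of it. For sitting, the policy exempts a type of bout that the item still counts. In both cases a room can change exactly as the policy asks and give the same answer before and after. A null result on these items could then be taken as failure of the policy.

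**Working it through.** The plan gives no figure for sitting or screen time to reproduce. Its power calculation (Sample size and power) uses time allocated for physical activity indoors and outdoors, so nothing there depends on this point. The check sets each item against the declared outcome and against its recommendation, then codes example days into the response categories of Table 3. The minutes in the examples are assumptions.

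**1. Sitting item against the declared outcome.** Let a day hold seated bouts b1, b2, …. The declared quantity is the sum of the bouts; the item records the largest.
- Room A, four bouts of 25 min: sum 4 × 25 = 100 min; largest 25 min; category 20–29 min.
- Room B, one bout of 25 min: sum 25 min; largest 25 min; category 20–29 min.

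The totals differ by a factor of 100/25 = 4 and the answers are identical. Two other Table 3 items concern limiting sedentary behaviour (cots, car seats and high chairs; strollers, swings and bouncers). Both use never-to-always scales and give no minutes. Screen time apart, no item yields daily sedentary minutes.

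**2. Sitting item against its recommendation.** Both are framed per bout, so they match in kind. The gap is the caregiver exemption.
- Before: bouts of 25 (with a caregiver, exempt), 25, 20 and 20 min. Sum 90 min; largest 25 min; category 20–29 min.
- After removing every non-exempt bout (25 + 20 + 20 = 65 min): sum 90 − 65 = 25 min; largest still 25 min; category 20–29 min.

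Counter-case: where the longest bout is non-exempt and falls from 60 min or more to under 60 min, the category does change.

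**3. Screen item against the declared outcome.** Screen time is named separately from sedentary time, and the item asks for its daily amount. These match.

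**4. Screen item against its recommendations.** For infants all screen use is discouraged, so total use is the right quantity. For toddlers and kindergarten children:
- 20 min non-learning + 0 learning = 20 min, category 15–29 min. Replaced by 0 + 20 = 20 min, category 15–29 min.
- 10 min non-learning + 15 learning = 25 min, category 15–29 min. Cut to 0 + 15 = 15 min, category 15–29 min.

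As a range: with 20 min/day at baseline and a non-learning share of 25% to 100%, between 0.25 × 20 = 5 and 1.00 × 20 = 20 min/day of barred use could be swapped one-for-one for learning use with a recorded change of 0. Counter-case: stopping all screen use moves the answer to 0 min, which does show compliance.

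**The case against.** The items come from established instruments, and the modified versions are reported to have acceptable test-retest reliability. That supports keeping their wording, but reliability does not turn a longest bout into a daily total.

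Several stronger readings are tempting, and the documents do not support them:
- A reader might infer that neither item measures a declared primary outcome. That fails for screens, because daily screen time is declared in its own right and is what the item asks for.
- A reader might infer that the sitting item misses its recommendation altogether. The recommendation is itself about time in one stretch, and no recommendation sets a daily sitting limit. The fourfold example counts against the outcome label and leaves the policy match untouched.
- A reader might infer that compliant and non-compliant rooms can never be told apart on screens. An answer of 0 min is unambiguous, and the no-change examples need a swap to learning use, or a cut too small to cross a category. Nothing in the protocol says how common these are.
- A reader might fault the meal-time exclusion because the policy reserves high chairs for eating. Table 2 marks that rule for infants only, while the sitting recommendation is for toddlers and kindergarten children.
- A reader might take the aim to mean increasing sedentary and screen time. Table 2 speaks of limiting sedentary behaviour and the sitting recommendation treats less as better, so this is a slip of wording.

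It is also fair to say that the power calculation and the primary-analysis sentence under Statistical analysis concern physical activity only, and that Table 3 prints the wording for any reader to see. These points limit the consequences. They do not remove the contradiction, because the Abstract, the aim, the Table 1 legend and the Primary outcomes section all name sedentary time as primary.

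**Conclusion.** The point holds in a limited form. For sitting, the protocol contradicts itself: it declares a daily amount and collects a maximum bout, so it cannot support a conclusion about daily sedentary time provided. This follows from the wording alone; the fourfold difference in total behind one answer is an illustration with assumed minutes. The missing caregiver exemption is a narrower imprecision in an item that otherwise suits its recommendation.

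For screens, the declared outcome is measured. What fails is the alignment statement for one recommendation: in toddler and kindergarten rooms a non-zero answer does not show whether barred use has stopped. The 5 to 20 min/day of unseen change rests on an assumed 20 min baseline and a one-for-one swap, and is not an estimate of what will happen.

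The sample size and the physical activity outcomes are untouched. The correction is worth making because it changes what the trial may conclude about a named primary outcome, at almost no cost.

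**What to change.** - **Sitting outcome.** Rename it the longest expected continuous seated bout, and remove the daily amount of sedentary time from the primary outcome and from planned conclusions. State that the item does not apply the caregiver exemption. Cost: wording only.
- **Existing items.** Keep both unchanged at baseline and follow-up. Adding the exemption to the sitting item after some services have been surveyed would mix a change of wording with true change in the time-by-intervention model.
- **Screen time.** Add one item on non-learning screen time for toddler and kindergarten rooms; the ages of children in the room are already collected. Where no baseline answer exists, compare arms at follow-up. The cost is one survey item and, for services already surveyed, no baseline adjustment. If the item is not added, limit the alignment statement and the conclusions to total screen time.
- **Aim.** Word it as increasing physical activity and decreasing seated-bout length and screen time. Cost: wording only.
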